#### **9.6. Event Schedule for each phase during enrollment:**

| Phase | Pre-Randomization | Post-Randomization |
|-------|-------------------|--------------------|
|-------|-------------------|--------------------|

| Period                                    | Screening | baseline | treatment |    |                |                  | Follow-up        |     |
|-------------------------------------------|-----------|----------|-----------|----|----------------|------------------|------------------|-----|
| Visit                                     | 1         | 2        | 3         | 4  | 5              | 6                | 7                | 8   |
| Day(s)                                    | -14 a -1  | 0        | 30        | 60 | 120            | 180              | 240              | 360 |
| Procedure                          |           |          |           |    |                |                  |                  |     |
| Informed Consent                          | x         |          |           |    |                |                  |                  |     |
| Randomization                             |           | x        |           |    |                |                  |                  |     |
| Clinical Record                           | x         |          |           |    |                |                  |                  |     |
| Previous/concurrent drugs                 | ←-----→   |          |           |    |                |                  |                  |     |
| Inclusion/Exclusion                       | x         | x        |           |    |                |                  |                  |     |
| Vital Signs                               | x         | x        | x         | x  | x              | x                | x                | x   |
| Complete physical exam                    | x         |          |           |    | x              |                  |                  | x   |
| Chest X-ray                               | x         |          |           |    | x              |                  |                  | x   |
| ECG                                       | x         |          |           | x  | x              | (x) e | (x) e | x   |
| 2D Echocardiogram                         | x         |          |           |    |                |                  |                  | x   |
| Pregnancy test                            | x         |          |           |    |                | x                | x                |     |
| Serology                                  | x         |          |           |    |                |                  |                  | x   |
| Laboratory                                | x         | x        | x         | x  | x              | x                | x                | x   |
| Quantitative PCR                          | x         |          |           |    | x d |                  |                  | x   |
| Biomarkers b                   |           | x        |           | x  | x              |                  |                  | x   |
| Focused Physical Examination c | x         | x        | x         | x  | x              | x                | x                | x   |
| Adverse Events                            |           |          | ←-----→   |    |                |                  |                  |     |
| Drug Accounting                           |           | x        | x         | x  | x              |                  |                  |     |

aLaboratory parameters will include: hemoglobin, total white blood cell count, differential white blood cell count, and platelet count. Laboratory biochemical parameters will include: CK, ALT, AST, GGT, alkaline phosphatase, total and direct bilirubin, a lipid profile: total cholesterol, c-HDL, and c-LDL, triglycerides, fasting blood glucose, and creatinine;

bBiomarkers: BNP, cTnT, IFN-γ, IL-1β, IL-4, IL-17A, e IL-10, sICAM-1, sVCAM-1, sE-selectin;

cPhysical examination focused only on the evaluation of adverse events.;

dPCR testing at these time points will be done with a single 10 ml sample;

eECGs will be performed at these visits only in case of previously identified abnormalities

### 9.7. Assessments:

On admission to the PCC, patients will undergo a complete medical history with an emphasis on CD, demographic data and medication history, physical examination, body weight and height, vital signs, and body temperature.

Ten ml of blood will be collected, in separate tubes, for hematological and biochemical evaluations: hemoglobin, total and differential white blood cell count, platelet count, CK, ALT, AST, GGT, alkaline

phosphatase, total and direct bilirubin, a lipid profile: total cholesterol, c-HDL, and c-LDL, triglycerides, fasting blood glucose and creatinine. A serum pregnancy test will also be performed. This test will be performed in the clinical laboratories of each center.

A 3 mL blood sample will be collected for conventional CD serology at each center's clinical laboratories and for a confirmatory serology test to be performed at the ISPCCH or an accredited laboratory.

5 mL of blood will be collected for qPCR. For clinical development and proof of concept, it has been proposed to use quantitative PCR parasitological tests as markers of efficacy in clinical studies of chronic indeterminate CD (Parrado et al., 2019). Thus, the real-time PCR technique described by Duffy et al. will be used in this assay (Duffy et al., 2013). Blood samples will be immediately added to a tube containing a volume (10mL) of a solution of guanidine/CIH 6M EDTA 0.2M 0.2M guanidine/CIH buffer 0.2M pH 8.0 (GEB) (Schijman et al., 2003). Samples with guanidine buffer can remain at room temperature for up to 30 days. For longer periods, it is necessary to store them in a refrigerator. After DNA extraction, samples will be processed using a commercial kit on an Applied 155 Biosystems 7300 RT-PCR system (Thermo Fisher).

An additional 3 ml of blood will be drawn for the biomarkers: BNP, cTnT, IFN- $\gamma$ , IL-1 $\beta$ , IL-4, IL-17A, and IL-10, sICAM-1, sVCAM-1, sE-selectin. These markers were selected following a literature review (Cortes-Serra et al., 2020; Echeverría et al., 2020; Llaguno et al., 2019). Serum levels of these markers will be determined using a multiplex approach with a Luminex 200 (R&Dsystems). To establish biological reproducibility, a pilot study will be performed before the sample analyses of this assay.

Finally, a baseline resting ECG and a 2D echocardiogram will be performed. Both tests will be performed at each center. The ECG should be normal or with nonspecific changes (incomplete right bundle branch block, incomplete left anterior fascicular block, mild bradycardia, minor PR interval widening, and minor ST-T changes). Any clinically significant abnormality found on the electrocardiogram will automatically lead to the exclusion of the patient from this study (see exclusion criteria).

After randomization and before starting treatments, patients will undergo a new focused physical examination, and blood will be drawn for qPCR and biomarker determination.

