|-------------------------------------------|---|---|---------|---|----------------|---|---|---|
| Serology                                  | x |   |         |   |                |   |   | x |
| Laboratory a                   | x | x | x       | x | x              | x | x | x |
| Quantitative PCR                          | x |   |         |   | x d |   |   | x |
| Biomarkers b                   |   | x |         | x | x              |   |   | x |
| Focused Physical Examination c | x | x | x       | x | x              | x | x | x |
| Adverse Events                            |   |   | ←-----→ |   |                |   |   |   |
| Drug Accounting                           |   | x | x       | x | x              |   |   |   |

aLaboratory parameters will include: hemoglobin, total white blood cell count, differential white blood cell count, and platelet count. Laboratory biochemical parameters will include: CK, ALT, AST, GGT, alkaline phosphatase, total and direct bilirubin, a lipid profile: total cholesterol, c-HDL, and c-LDL, triglycerides, fasting blood glucose, and creatinine;

bBiomarkers: BNP, cTnT, IFN- $\gamma$ , IL-1 $\beta$ , IL-4, IL-17A, e IL-10, sICAM-1, sVCAM-1, sE-selectin;

cPhysical examination focused only on the evaluation of adverse events.;

dPCR testing at these time points will be done with a single 10 ml sample;

eECGs will be performed at these visits only in case of previously identified abnormalities

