Although our preclinical studies were performed with simvastatin, we propose atorvastatin (ATO) as an experimental statin. As simvastatin is associated with ezetimibe, it will not be considered in this study. ATO's therapeutic and safety profiles are well known, as well as its mechanism of action and pharmacological actions, including its anti-inflammatory properties, which are shared by the other members of the statin class. Due to the low incidence of severe AEs and its efficacy, ATO is one of the most widely used statins. 20-80 mg/day of ATO are used to lower the so-called LDL cholesterol, implicated in the pathogenesis of the atherosclerotic cardiovascular disease. However, a clinical phase II proof-of-concept study is imperative because i) it is a way to translate the results obtained in the animal model, and ii) a minimum effective dose and safety need to be evaluated in the context of the patient undergoing treatment of chronic CD and, most importantly, iii) because statins are not currently approved for the treatment of CD.

Considering i) the high burden of disease; ii) the role of the endothelium and inflammation in the initiation and propagation of vascular wall injury in CD; iii) that current therapy for CD in the chronic phase is unsuccessful and increases the risk of systemic toxicity, AEs, and poor compliance; iv) that improving the efficacy of current antichagasic drugs by modifying host responses would make current treatment more effective; v) that preclinical evidence suggests that statins may have a role in preventing cardiac damage in CD; vi) that statins are safe and with a well-known pharmacological profile; then, a combination of trypanocidal drugs with those that induce resolution of the inflammatory process resulting from parasite persistence could be an effective therapeutic strategy to prevent the chronic consequences of CD. Consequently, it is proposed that the following hypothesis:

**In patients with chronic Chagas disease, statins improve the efficacy of antiparasitic treatment by decreasing inflammation and improving endothelial and cardiac function**

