## 9.3. Study description:

This is a proof-of-concept Phase II clinical trial with three different groups: Two groups will receive antichagasic therapy plus 40 or 80 mg/day of ATO. The third group will receive a placebo plus antichagasic therapy. The placebo is justified as long as the patient receives the complete conventional antichagasic treatment; therefore, the management of his Chagas disease is assured. In this clinical trial, the placebo will be a nutritional supplement tablet with an appearance similar to that of ATO. This product was chosen given the potential difficulties in manufacturing a small number of pills since the trial does not have a pharmaceutical industry sponsor capable of manufacturing it under Good Manufacturing Practice standards.

Nutritional supplements do not affect vascular or cardiac inflammatory parameters and therefore do not introduce confounding elements in the comparative analysis with atorvastatin.

Patients will first receive conventional antichagasic therapy for two months. After two weeks (or until normalization of liver enzymes), treatment with atorvastatin or placebo will be initiated for

four months. These doses were chosen to minimize false negative results, thus providing the best hypothesis test and maximizing the pharmacodynamic effect on inflammation and cardiac and endothelial function. In addition, the treatment sequence aims to minimize adverse reactions that could be caused by the eventual combination of antichagasic drugs with atorvastatin. Study subjects will be randomized, and the three groups will be double-blinded (both clinical investigators and subjects will be blinded) to ATO or placebo. However, antichagasic therapy will be open-labeled. In addition, qPCR and the other laboratory evaluations, as well as ECGs and 2D echocardiograms, will be performed with the clinical investigators blinded to ATO or placebo allocation.

This study will be conducted in four centers: 1) Hospital San Juan de Dios and 2) Hospital Felix Bulnes in Santiago, Metropolitan Region, 3) Hospital [name] in Viña del Mar, 4) Hospital San Martin de Quillota, Valparaiso Region. Each center annually admits 60 new patients to its Chagas Control Program (CCP). These four centers are part of the care network of the National Chagas Disease Control Program.

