#### **11.2. Adverse events and withdrawal from the study**

##### **11.2.1. Adverse events:**

An AE will be defined as any adverse medical event (any unfavorable and unintended symptom, sign, or disease, including an abnormal laboratory or ECG finding) or worsening of any pre-existing condition occurring during the study, whether or not considered causally related to the study or study drugs. Abnormal laboratory (hematology and biochemistry) results will be reported as an AE if they: a) occur or worsen after initiation of study treatments, b) are considered a clinically significant adverse change by the clinical investigator, or c) are higher than Common Terminology Criteria for AEs (CTCEA) grade 1 (National Cancer Institute (USA), 2017), unless associated with an already reported clinical AE.

Clinical investigators, or appropriate site personnel (not involved in the study), will screen any subject experiencing an AE as soon as possible. The investigator will do whatever is medically necessary for the safety and well-being of the subject. The subject will remain under observation while receiving any trial drug and for two months following the last day of drug administration, or longer if medically indicated in the investigator's opinion. All AEs observed or reported after administration of investigational treatments will be followed until resolved or until medically stable.

For this study, the clinical investigators at each center will report to the principal investigator, who, in turn, will be responsible for reporting AEs to the Ethics Committees of the Centers and the Human Research Ethics Committee of the Faculty of Medicine of the University of Chile and the clinical trials section of the ISPCH. Clinical investigators should report all directly observed AEs and all those spontaneously reported by subjects, using concise medical terminology. In addition, during each trial visit, subjects will be interviewed and undergo a specific physical examination for the evaluation of AEs. All adverse events should be recorded in the subject's clinical record and an ad hoc database.

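### Lipid results taken during atorvastatin/placebo dosing are not withheld from the blinded investigators, so the blind is not protected

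*Protocol*

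**What the plan says.** **Blinding.** Protocol Section 9.3 states that "the three groups will be double-blinded (both clinical investigators and subjects will be blinded) to ATO or placebo". It adds that qPCR, the other laboratory evaluations, ECGs and echocardiograms "will be performed with the clinical investigators blinded to ATO or placebo allocation". The comparator is masked by appearance: "the placebo will be a nutritional supplement tablet with an appearance similar to that of ATO". Section 11.2.6 reserves opening the blind for rare emergencies and unexpected severe events.

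**What is measured.** The Study Flowchart and Section 9.6 mark the laboratory row at all eight visits: screening and days 0, 30, 60, 120, 180, 240 and 360. Footnote a puts CK, transaminases and bilirubin in the same panel as "a lipid profile: total cholesterol, c-HDL, and c-LDL, triglycerides, fasting blood glucose, and creatinine". Section 9.7 lists that panel for admission, mentions a serum pregnancy test, and continues: "This test will be performed in the clinical laboratories of each center".

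**What the drug does.** Section 7.2 says "20-80 mg/day of ATO are used to lower the so-called LDL cholesterol". That range covers both trial doses, 40 and 80 mg.

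**Who uses the results.** Under Section 11.2.1 one ground for reporting laboratory results as adverse events is that they "are considered a clinically significant adverse change by the clinical investigator". Section 11.2.4 has the investigator judge relatedness, weighing among other things how patients are known to respond to statins, and leaves suspension and discontinuation to the clinical investigator. Section 11.2.5 names ALT, bilirubin and CK as possible reasons for withdrawal. Section 16.2 has the investigator keep laboratory reports as source documents.

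No section masks, withholds or redirects lipid results.

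**The concern.** A double blind can fail through a laboratory report as easily as through a tablet that looks different. Here the panel that investigators need for safety (CK, ALT, bilirubin) also carries a known pharmacodynamic marker of the test drug. The marker would be easy to read. Section 10.2 excludes anyone previously treated with a statin, and the panels at screening and on days 0, 30 and 60 all precede the masked drug. Each patient therefore has up to four statin-naive values for comparison.

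The decisions most exposed are those the protocol gives to the same investigators: whether an event is related to the drug, and whether treatment is paused or stopped. Safety is part of the primary goal (Section 8.1), and discontinuation is a listed safety measure (Section 8.2.2). If either is judged with a guess at the arm in mind, the between-group safety comparison is distorted, and no later analysis can repair it.

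**Working it through.** The plan states no figure on this point, so there is none to reproduce. Two checks were made.

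**1. Which lipid panels fall on drug?** Inputs: 60 days of antichagasic treatment (Section 7.1.4), a gap of two weeks or until liver enzymes normalise (Section 9.3), and the visit days in Section 9.6.

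- Earliest start of atorvastatin/placebo: 60 + 14 = day 74.
- Eight weeks of dosing (Section 9.5 and the Summary's duration paragraph; the Summary's study design says two months): 74 + 56 = day 130. Only day 120 is on drug.
- Four months (Section 9.3), taken as 120 days: 74 + 120 = day 194. Days 120 and 180 are on drug.
- Days 240 and 360 are off drug under both durations when dosing starts at day 74. A delayed start moves these windows later.

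The stated durations contradict each other and must be reconciled. Under either one, with the earliest start, at least one panel is on drug.

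**2. How well could one on-treatment LDL value separate the arms?** The documents give neither the size of the LDL fall nor its variability, so both are assumed: mean change 0% on placebo, mean fall m of 20-50% on atorvastatin, and SD s of the within-patient percentage change of 10-25 points, normal and equal in both groups. With the cut-off at the midpoint m/2, the proportion correctly classified is the same in each group: Phi(m / (2s)).

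| Mean fall m | s = 10 | s = 15 | s = 20 | s = 25 |
|---|---|---|---|---|
| 20% | 0.841 | 0.748 | 0.691 | 0.655 |
| 30% | 0.933 | 0.841 | 0.773 | 0.726 |
| 40% | 0.977 | 0.909 | 0.841 | 0.788 |
| 50% | 0.994 | 0.952 | 0.894 | 0.841 |

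Lowest: Phi(20/50) = Phi(0.4) = 0.655, about 66%. Highest: Phi(50/20) = Phi(2.5) = 0.994, about 99%.

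**Benchmark.** With 100 patients per group, two of three receive atorvastatin. Calling every patient atorvastatin is right in 200/300 = 67% overall: all of the atorvastatin patients and none of the placebo patients, an average of (100 + 0)/2 = 50% across the two kinds of patient. The cut-off is right in the same share of both kinds, so its overall accuracy equals the table entry. Fifteen of the 16 entries exceed 67%. The exception, 0.655, is no better than the blanket guess in overall count, although it still gets 66% of placebo patients right.

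**The case against.** The strongest case against is that this argues from silence. The protocol nowhere says that lipid results go to blinded staff, and Section 9.3 says that laboratory evaluations are done with investigators blinded to allocation. That sentence, however, concerns knowledge of the assignment and does not address a result that reveals it. Sections 11.2.1, 11.2.5 and 16.2 put the panel's results in investigators' hands without exempting lipids.

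Five stronger readings are tempting, and the documents do not support them.

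- *The panel is shown to be run at each site.* The sentence in Section 9.7 is singular, follows the pregnancy test and describes admission. It does not settle where later lipids are measured.
- *Every visit after the start is revealing.* Lipids are drawn at all of them, but the clear signal is confined to on-drug panels. The documents say nothing on how long an LDL effect lasts after dosing ends.
- *The double blind has failed.* Classification is probabilistic, nobody is shown to have been unblinded, and at the weakest assumptions the overall gain over a blanket guess disappears.
- *The primary outcome is biased.* Section 9.7 places the baseline ECG and echocardiogram at each centre, but no section says who reads the day-360 tests or assigns the stage, or whether that person sees lipids. The risk is possible, not established.
- *LDL reveals the dose.* Nothing in the documents allows 40 mg to be told from 80 mg.

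**Conclusion.** The point holds in limited form: as scheduled, the trial gives investigators who are meant to be blinded a marker that can suggest atorvastatin versus placebo, so the blind is promised but not protected. The exposure is one panel (day 120) or two (days 120 and 180), depending on which stated duration applies and on a start near day 74. Its strength, about 66-99% correct in each group, rests wholly on assumed LDL falls and SDs and should be read against the 67% benchmark. The best-supported consequence is bias in adverse-event attribution and discontinuation. The change is worth making before lipid results from dosing visits reach the sites, because unblinding cannot be undone.

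**What to change.** State in Sections 9.3, 9.6 and 9.7 that, from the first visit after atorvastatin/placebo starts, total cholesterol, HDL, LDL and triglycerides are left off the reports sent to site investigators, patients and outcome readers, and are held by the laboratory until database lock. CK, liver tests and the other safety results continue to be released. Reconcile the stated dosing durations so that the on-drug visits are clear.

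The cost is a reporting instruction covering the four centres; no new unblinded role is needed. The downside is that sites do not see lipid values during follow-up. No listed endpoint and no named withdrawal criterion uses them, and the stored values remain available for the laboratory tabulations in Section 12.5. Because Section 11.2.1 covers biochemistry generally, it should say how lipid abnormalities are handled while the results are held.

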|                                                             | A                                                                                                                                       | B1                                                                                                                                                                                                           | B2                                                                                                                                               | C                                                                                                        | D                                                                                                                           |
| Patients with findings compatible with acute Chagas disease | Patients at risk for developing CHF. They have positive serology, neither structural cardiopathy nor CHF symptoms. No digestive changes | Patients with structural cardiopathy, evidenced by electrocardiographic or echocardiographic changes, but with normal global ventricular function and neither current nor previous signs and symptoms of CHF | Patients with structural cardiopathy characterized by global ventricular dysfunction, and neither current nor previous signs and symptoms of CHF | Patients with ventricular dysfunction and current or previous symptoms of CHF (NYHA FC I, II, III or IV) | Patients with refractory symptoms of CHF at rest, despite optimized clinical treatment, requiring specialized interventions |

Arq Bras Cardiol 2011; 97(2 supl.3): 1-48

The **secondary outcome** is determined by the change in plasma levels of biomarkers versus changes in parasite load.

Additional measures of scientific value: (a) change in plasma levels of biomarkers of inflammation and endothelial activation; (b) incidence and severity of AEs; (c) change in parasite burden and serologic response over the follow-up period, measured by quantitative PCR (qPCR); (d) changes in biomarker levels at different follow-up time points and correlation with parasite burden and ATO regimen; and (e) incidence of treatment discontinuation due to severe AEs.

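### The text orders a pre-treatment qPCR sample that both schedule tables omit, and the qPCR blood volume is not settled across visits

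*Protocol*

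**What the plan says.** Section 9.7 closes with an instruction for the interval between randomization and the start of treatment: patients have another focused physical examination, and "blood will be drawn for qPCR and biomarker determination". In both schedule tables (Summary flowchart and section 9.6) the row "Quantitative PCR" is marked at visit 1 (screening), visit 5 (day 120) and visit 8 (day 360). Visit 2 (day 0) is blank.

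On volume, section 9.7 states, among the admission assessments, "5 mL of blood will be collected for qPCR". The blood goes into "a tube containing a volume (10mL) of a solution" of guanidine buffer. Footnote d of both tables reads "PCR testing at these time points will be done with a single 10 ml sample". It speaks of time points in the plural, but the mark stands only at day 120. No blood volume is given for day 0 or day 360.

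A positive qPCR is an entry criterion (Summary and section 10.1). Section 9.1 defines the secondary outcome as "the change in plasma levels of biomarkers versus changes in parasite load". Section 8.2.3 also lists treatment response by qPCR as a secondary goal. No section names the qPCR sample that serves as baseline.

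**The concern.** Change in parasite load is a within-patient quantity, so it needs a sound pre-treatment value and comparable samples afterwards. If the only pre-treatment value is the one that had to be positive for entry, part of any later fall is regression to the mean. Some patients whose true load has not changed will test negative on repeat and be counted as cleared.

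The protocol describes the setting where this matters: section 7.1.3.1 calls parasitemia in the chronic phase typically low, and section 7.1.2 warns that a negative PCR does not rule out persistence. A larger blood volume at a later visit could push detection the other way.

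At stake are the absolute clearance rates, the size of the within-patient change, and the biomarker-parasite analyses planned in section 12.4. With four centers, some may follow the text and others the tables.

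**Working it through.** The protocol states no figure on this point that could be reproduced. The check is a comparison of sections, followed by an illustration on assumed values.

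**1. The pre-treatment draw.** The sentence in section 9.7 names three procedures between randomization and treatment, which is visit 2 in the tables.
- Focused physical examination: marked at visit 2 in both tables.
- Biomarkers: marked at visit 2 in both tables.
- qPCR: in the text, absent from visit 2 in both tables.

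Text and tables agree on two of the three items and conflict on the third. This contradiction needs no assumption.

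**2. The volumes.**
- Admission: 5 mL of blood (section 9.7).
- Day 0: none stated.
- Day 120: one 10 mL sample (footnote d).
- Day 360: none stated, and no footnote mark.

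The buffer figure does not reconcile 5 with 10: 5 mL of blood plus 10 mL of buffer makes 15 mL. The ratio between the stated blood volumes is 10/5 = 2.

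**3. Illustration of selection (assumed values).** The protocol gives no load distribution. Assume that the targets detected in V mL are Poisson with mean λV, and that λ varies between patients as a gamma variable with mean m per mL and shape k. Take patients with at least one target in 5 mL at screening, then repeat the test with λ unchanged.

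Worked case, k = 1 and m = 0.1:
- P(screen positive) = 1 − 1/(1 + 5m) = 1 − 1/1.5 = 0.333
- Mean measured load at screening, given positive = m/0.333 = 0.300 per mL
- Mean load on repeat = [m − m/(1 + 5m)²]/0.333 = (0.100 − 0.0444)/0.333 = 0.167 per mL
- Apparent fall with no true change = 1 − 0.167/0.300 = 44%

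Simulation over k from 0.3 to 2, with no true change:
- m = 0.1: fall 28–51%; repeat 5 mL test positive in 46–60%
- m = 0.3: fall 10–19%; positive in 75–77%
- m = 1: fall 2–3%; positive in 87–94%

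The artefact is large at low loads and almost gone at 1 per mL.

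**4. Illustration of volume (assumed values).** Assume further that the assayed volume scales with the drawn volume. Then P(detect) = 1 − exp(−λV), at 5 mL and 10 mL:
- λ = 0.02: 9.5% and 18.1%
- λ = 0.1: 39.3% and 63.2%
- λ = 0.2: 63.2% and 86.5%
- λ = 1: 99.3% and 100%

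The gap is exp(−5λ) − exp(−10λ). It peaks where exp(−5λ) = 0.5, at 0.50 − 0.25 = 25 points. If a fixed aliquot is extracted at every visit, the gap is zero.

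**5. Both together at day 120.** In the same simulation, screen-positive patients with unchanged load test positive on a 10 mL sample in 67–77% (m = 0.1), 88–90% (m = 0.3) and 93–99% (m = 1). The larger volume offsets part of the selection effect but does not remove it.

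**The case against.** The strongest reply has five parts.

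First, a site that follows section 9.7 will have a pre-treatment sample that played no part in selection, and naming the baseline among two samples is ordinary analysis-plan work. The first half stands: the selected baseline arises only if the tables govern. The second half stands only in part. An analysis plan can choose between samples, but it cannot recover one that was never drawn.

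Second, the 5 mL belongs to admission and the 10 mL to day 120. These are different visits, so the two figures do not contradict each other for one sample. This stands. What remains is an unexplained difference, a footnote in the plural with one mark, and two visits without a volume.

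Third, drawn volume is not assayed volume, and the protocol gives neither an extracted volume nor a detection limit. This stands. A reader might infer that detection limits do differ between visits; the documents support this only as a conditional. Reporting per mL would also deal with much of the difference for samples that can be quantified, though not for negatives.

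Fourth, selection and volume act alike in three blinded, randomized arms, and parasite load is not the primary outcome. This stands. A reader might infer that atorvastatin versus placebo is biased; it is not, on this ground.

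Fifth, a day 0 baseline will be undetectable in some patients, and no fall can be measured from it. This is a real cost and belongs with the fix.

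**Conclusion.** The point holds in a limited form. The conflict over the day 0 qPCR sample is certain, appears in both tables, and decides whether a sample is collected. If the tables are followed, the only pre-treatment parasite load is one selected for positivity, and within-patient change and absolute clearance rates would include regression to the mean. The volume specification is incomplete and ambiguous; it would make sensitivity differ between visits only if the assayed volume follows the drawn volume.

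The documents do not fix the size of either effect. The ranges shown rest on Poisson sampling, an assumed gamma spread of loads and, for volume, proportional assaying. No calculation was made of the effect on the biomarker-parasite association, so no size or direction is claimed for it. It would go too far to say that the parasite-load outcome does rest on a selected baseline and unequal detection limits, because both depend on conditions that the protocol leaves open. The correction is worth making because the outcome is a stated secondary one and an undrawn sample cannot be replaced.

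**What to change.** - Mark qPCR at visit 2 in the Summary flowchart and in section 9.6, as section 9.7 already states.
- Name that sample as the main baseline for change in parasite load. Keep the screening value for eligibility, and use it as baseline in a sensitivity analysis.
- State one blood volume and buffer ratio for every qPCR visit, or a fixed extracted volume, and correct footnote d and its mark to match.

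The cost is a correction to two tables and a footnote, plus up to 300 further assays (one per planned patient) on a draw that the text already includes. Some patients will have an undetectable day 0 value: on the assumptions above with 5 mL, 40–54% at m = 0.1, 23–25% at m = 0.3 and 6–13% at m = 1 (one minus the repeat-positive rates). The analysis must say how these patients are handled, and the sensitivity analysis on the screening value is useful for that reason too.
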